## Abstract

**Introduction:**

Environmental enteric dysfunction (EED) is a subacute inflammatory condition of the small intestinal mucosa with unclear aetiology that may account for more than 40% of all cases of stunting. Currently, there are no universally accepted protocols for the diagnosis, treatment and ultimately prevention of EED. The Bangladesh Environmental Enteric Dysfunction (BEED) study is designed to validate non-invasive biomarkers of EED with small intestinal biopsy, better understand disease pathogenesis and identify potential therapeutic targets for interventions designed to control EED and stunting.

**Methods and analysis:**

The BEED study is a community-based intervention where participants are recruited from three cohorts: stunted children aged 12–18 months (length for age Z-score (LAZ) <−2), at risk of stunting children aged 12–18 months (LAZ <−1 to −2) and malnourished adults aged 18–45 years (body mass index <18.5 kg/m^2^). After screening, participants eligible for study provide faecal, urine and plasma specimens to quantify the levels of candidate EED biomarkers before and after receiving a nutritional intervention. Participants who fail to respond to nutritional therapy are considered as the candidates for upper gastrointestinal endoscopy with biopsy. Histopathological scoring for EED will be performed on biopsies obtained from several locations within the proximal small intestine. Candidate EED biomarkers will be correlated with nutritional status, the results of histochemical and immunohistochemical analyses of epithelial and lamina propria cell populations, plus assessments of microbial community structure.

**Ethics and dissemination:**

Ethics approval was obtained in all participating institutes. Results of this study will be submitted for publication in peer-reviewed journals.

**Trial registration number:**

ClinicalTrials.gov ID: NCT02812615. Registered on 21 June 2016.

Strengths and limitations of this studyThis study will compare a wide array of non-invasive biomarkers of environmental enteric dysfunction (EED) to the diagnostic gold standard: intestinal histopathology.A histological scoring system will be developed for identifying EED and describing its severity.This study will be one of the largest community-based nutritional interventional studies in improving the growth parameters in children with stunting.Due to ethical reasons, collecting small intestinal tissue from healthy population of the same community will not be possible.‘Failure to thrive’ criterion was selected based on assumptions as no data were available.

## Introduction

Environmental enteric dysfunction (EED), previously known as tropical enteropathy and environmental enteropathy, is a subacute inflammatory condition of the small intestinal mucosa with unclear aetiology. EED has been associated with a variety of environmental exposures and host factors and is implicated in growth faltering.^1^ Linear growth faltering typically occurs within the first 2 years of life and after this period, it is difficult to reverse.^2^ Globally, there are more than 160 million stunted children (length for age Z-score (LAZ) <−2).^3^ Previous work in Gambia has revealed that 43% of observed growth faltering was associated with evidence of small intestinal enteropathy.^4^ There are no universally accepted protocols for the diagnosis and treatment of EED. The main impediments are a paucity of validated non-invasive biomarkers of small intestinal health, a lack of understanding of the pathologic state of the small intestine in EED and rudimentary knowledge of disease mechanisms.^5^ While there are several candidate surrogate biomarkers of EED, to our knowledge none of these non-invasive biomarkers have been directly correlated with the diagnostic gold standard: intestinal histopathology. The Bangladesh Environmental Enteric Dysfunction (BEED) study, a community-based intervention study, is designed to validate candidate non-invasive biomarkers of EED and to identify potential therapeutic targets for interventions. This report describes the BEED study design, including the biospecimens and data types that are being collected for analyses.

## Methods and analysis

The protocol for the BEED study (ClinicalTrials.gov identifier NCT02812615) was developed through a collaborative effort among International Centre for Diarrhoeal Disease Research, Bangladesh (icddr,b), Dhaka Medical College and Hospital (DMCH), Bangabandhu Sheikh Mujib Medical University (BSMMU), Dhaka, Dhaka Shishu Hospital, Dhaka, Apollo Hospitals, Dhaka, Bangladesh, University of Virginia, USA and Washington University, USA. The study is funded by the Bill and Melinda Gates Foundation under its Global Health Program (http://www.gatesfoundation.org/How-We-Work/Quick-Links/Grants-Database/Grants/2015/11/OPP1136751). Enrolment has been initiated and is expected to continue until December 2018.

### Objectives

The goals of this study are to (1) develop a histological scoring system for identifying EED and describing its severity; (2) employ this scoring system to test the validity of proposed, candidate non-invasive biomarkers of EED and identify novel biomarkers; (3) test the degree of correlation between EED score and nutritional status defined by anthropometry; (4) determine the role of the gut microbiota in the pathogenesis of EED, in part through transplantation of luminal/mucosal proximal small intestinal and faecal microbiota from malnourished children with and without histopathological evidence of EED into gnotobiotic mice to directly test transmissibility of gut barrier/mucosal immune, growth and metabolic phenotypes and (5) characterise biological pathways that operate in the host and/or gut microbiota that are associated with EED to identify potential therapeutic targets.

### Study settings and participants

The overall design of the BEED study is illustrated in figure 1. There is a community-based nutrition intervention group and a comparison group. In the nutrition intervention group, participants are being recruited from two age groups: a child cohort (age 12–18 months) and an adult cohort (age 18–45 years). The child cohort consists of individuals who are stunted (LAZ <−2) and those who are at risk of stunting (LAZ <−1 to −2). These two subgroups will be used to compare histopathological features of EED with LAZ scores. The adult cohort consists of malnourished individuals (body mass index (BMI) <18.5 kg/m^2^) who will provide an opportunity to further explore the association between body mass (in this case low BMI) and the pathological features of EED and also critically assess the degree to which histopathological features of EED in children manifest in adults.

**Figure 1 F1:**
[figure not shown]
Study design of Bangladesh Environmental Enteric Dysfunction study. GI, gastrointestinal.

The BEED study is recruiting two control groups in order to compare the histological features in their duodenal mucosal biopsies with those of documented in cases of EED. Due to obvious ethical considerations, it is not possible to collect small intestinal biopsy samples from entirely healthy and asymptomatic subjects. Therefore, biopsies are being collected from children who are neither stunted nor suffering from EED and who undergo upper gastrointestinal (UGI) endoscopy as part of their clinical care. This control group of children are being recruited by the collaborators at the University of Virginia Hospital in Charlottesville, Virginia, USA. An equal number of age-matched and sex-matched healthy adult controls (BMI >18.5) suffering from functional dyspepsia who have no evidence of any organic diseases are being recruited from the Gastroenterology Outpatient Department of DMCH and the icddr,b Staff Clinic and undergo UGI endoscopy.

Following application of the inclusion/exclusion criteria listed in online supplementary file 1, undernourished children and adults are receiving nutrition and health interventions (table 1). Participants who fail to respond to nutritional therapy are considered eligible for UGI endoscopy with mucosal biopsies. Candidate EED biomarkers are being measured in faeces, urine and plasma samples collected from participants once before and once after the nutritional intervention.

10.1136/bmjopen-2017-017768.supp1Supplementary data

**Table 1 T1:** Nutrition and health interventions

Intervention	Delivery method
Egg	One egg daily, 6 days a week for either 2 months (children at risk for stunting and malnourished adults) or 3 months (stunted children)
Milk	150 mL whole milk daily, 6 days a week for either 2 months (children at risk for stunting and malnourished adults) or 3 months (stunted children)
Micronutrient sprinkles	–Parents will be given one sachet of multiple micronutrient sprinkles per day to be administered to the child at home with the midday meal for 2 months –Each sachet contains one recommended dietary allowance (RDA) of vitamin A, vitamin C, folic acid, iron and zinc
Nutritional counselling	Parents/caregivers will be provided with nutritional counselling with particular emphasis on adding vegetable oil to the cooked diet as a source of energy as well as sources of animal-based products, such as small fish or chicken meat, and so on along with regular intake of vegetables
Antihelminthic treatment	–As per national guidelines –If participants have not been treated for helminths in the preceding 3 months, will get either 200 mg of albendazole or 10 mg/kg pyrantel pamoate single dose
Treatment	Intercurrent illnesses

The BEED study is conducted among residents of Mirpur, one of the 21 administrative units of the nation’s capital, Dhaka. The Mirpur area is located 7–8 km from the icddr,b Dhaka Hospital at Mohakhali. Mirpur has a population of ~500 000 living in an area of 14.22 km^2^: that is, the population density is more than 38 000 people per square kilometre. The detailed socioeconomic and demographic information of the study location has been published elsewhere.^6^

### Sample size

Participants are being recruited in a cross-sectional manner. Sample size calculations were predicted on the following assumptions: prevalence of stunting at our study site is 40%; after receiving nutrition intervention ~20% will fail to manifest improved linear growth; only one-third will give their consent for endoscopy and 90% of the stunted children will have one or more abnormal gut biomarkers with a precision of 10% and 95% CI. Using the formula n=(Z_1−α/2_)^2^×P×(1−P)/d^2^, where n is the required sample size without attrition; P is the prevalence of one or more abnormal gut biomarker in stunted children=90% or 0.9; d is the level of actual precision=10% or 0.1; Z_1−α/2_ is the value for standard normal distribution at 95% level of significance=1.96, a minimum of 35 stunted children, 35 children at risk of stunting and 35 malnourished adults will be needed for UGI endoscopy and biopsy. Therefore, the final sample size for endoscopy is 105 subjects (35+35+35). As endoscopy is an invasive procedure, we assume that only one-third of those who will fail to respond after nutrition intervention will give consent for the procedure. As a consequence, the ‘basic’ sample size was increased threefold for a minimum of 105 (35×3) stunted children, 105 (35×3) children at risk of stunting and 105 (35×3) malnourished adults. To achieve this goal, 525 stunted children, 525 children at risk of stunting and 525 malnourished adults will be recruited for nutrition interventions, based on the assumption that ~20% of each group will fail to respond despite the nutritional intervention. To enrol the desired numbers of participants, at least 3977 (1312+2665) children 12–18 months old and 2100 adults needed to be surveyed based on the current prevalence of malnutrition in both the age groups. An equal number (35) of age-matched and sex-matched apparently healthy adult controls (BMI >18.5) will be recruited from the outpatient department of DMCH and icddr,b Staff Clinic. Apart from the dyspeptic symptoms by Rome III criteria,^7^ these subjects will have no other symptoms.

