### Indications for and details of the procedures used for UGI tract endoscopy and mucosal biopsy

After completion of nutritional therapy, all enrolled participants are assessed for responses. Definitions of ‘failure to thrive/respond’ are as follows:LAZ score remains <−2 for members of the stunted children cohortLAZ score remains <−1 for the ‘at risk of stunting’ children cohortBMI <18.5 kg/m^2^ and <10% increase in BMI for those in the adult cohort

Participants who meet the study definition of ‘failure to thrive/respond’ are further checked for the presence of any secondary cause of malnutrition such as tuberculosis, any parasitic infection, and so on. If nothing conclusive is found, the participant may undergo preparations for UGI endoscopy with biopsy. Participants with celiac disease (as defined by tissue transglutaminase IgA, and clotting disorders (determined by prothrombin time/International normalised ratio (INR) coagulopathy tests) will be excluded from the study. There is no published information about the prevalence of celiac disease in Bangladesh from any representative sample.^16^ One study of hospitalised adult patients with irritable bowel syndrome observed that the prevalence of celiac disease was 9%.^17^ In the BEED study, immediate test results for celiac disease are not available; therefore, we are unable to screen out individuals with this disorder before nutrition intervention is initiated. Nonetheless, BEED will screen 1575 participants for celiac disease; as such, it will be the first study in Bangladesh to explore the prevalence of this disorder in a paediatric population. Necessary management and counselling is provided to the participants suffering from celiac disease or clotting disorders.

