### Protocol timeline

The overall schedule for enrolment, interventions and assessments, including UGI endoscopy and biopsies, is described in table 4.

**Table 4 T4:** Schedule of enrolment, interventions and assessments

	Study period							
	Enrolment	Preintervention	Nutrition intervention			Postintervention assessment	Eligibility assessment for UGI endoscopy	UGI endoscopy and biopsy
Timepoint	***−T_1_***	0	Month 1 (***T_1_***)	Month 2 (***T_2_***)	Month 3 (***T_3_***)	Week 1 (***T_4_***)	Week 2 (***T_5_***)	Week 3 (***T_6_***)
Enrolment	X							
Pre-enrolment survey	X							
Eligibility screen	X							
Informed consent	X						X	
Interventions								
Stunted children								
Children at risk of stunting								
Malnourished adult								
Assessments								
SES, WASH, FFQ		X				X		
Anthropometry*		X	X	X	X	X		
Blood biomarkers		X				X		
Stool biomarkers and TAC		X				X		
Microbiota		X				X		
Urine L:R		X				X		
Breath SIBO		X				X		
UGI endoscopy and biopsy		X				X		
Histopathology, IHC, morphometry								X

*Anthropometry done fortnightly.

IHC, immunohistochemistry; L:R, lactulose/rhamnose; SIBO, small intestinal bacterial overgrowth; TAC, TaqMan Array Card; UGI, upper gastrointestinal; SES, socio-economic status; WASH, water-sanitation-hygiene; FFQ, food frequency questionnaire.

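### The 20% non-response rate behind 525 recruits per cohort describes lack of growth improvement, but in children the failure rule in use counts everyone still below the entry LAZ cut-off

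*Protocol article*

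**What the plan says.** The Sample size section of the protocol article lists among its assumptions that "after receiving nutrition intervention ~20% will fail to manifest improved linear growth". Further on it uses the same figure as the divisor for all three cohorts, so that "525 stunted children, 525 children at risk of stunting and 525 malnourished adults will be recruited for nutrition interventions". There the reason for the number is worded differently, namely "based on the assumption that ~20% of each group will fail to respond despite the nutritional intervention". One-third of non-responders are expected to consent to endoscopy, which gives the 35 biopsied participants per cohort.

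The section on indications for endoscopy and biopsy defines failure to respond. For the first child cohort it is "LAZ score remains <−2 for members of the stunted children". For at-risk children the rule has the same form, with −1 as the cut-off. Neither child rule refers to change. The adult rule requires a final BMI below 18.5 kg/m² "and <10% increase in BMI for those in the adult cohort".

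The strengths and limitations list says of the failure criterion that the "criterion was selected based on assumptions as no data were available". The Dietary supplementation section expects incremental growth improvement in children and gives no size for it.

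**The concern.** Failing to improve and remaining below a cut-off are different events. A child who moves from LAZ −3.5 to −2.1 has gained 1.4 Z, so is not among the 20% in the Sample size section, yet is a failure under the rule in use. A child who moves from −2.02 to −1.98 is a responder on a gain of 0.04 Z.

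Two things are at stake. The first is planning: the expected numbers of non-responders and endoscopy candidates, and the recruitment figure derived from them, rest on a rate for another event. The second is who supplies the tissue. The failure rule decides who is offered endoscopy, and so whose histology the biomarkers are validated against. If the rule captures many children who improved, the biopsied group is not the one the sample-size text describes.

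**Working it through.** **1. The plan's own chain.** Inputs from the Sample size section: P = 0.9, d = 0.1, z = 1.96, consent one-third, non-response 20%, stunting prevalence 40%.

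- n = 1.96² × 0.9 × 0.1 / 0.1² = 34.57, rounded up to 35
- 35 × 3 = 105 non-responders
- 105 / 0.20 = 525 recruits
- 525 / 0.40 = 1312.5, given as 1312 stunted-cohort children to survey

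Every step reproduces. The question is only whether 0.20 is the right input.

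**2. Gain needed for 20% failure under the rule in use.** The documents give no LAZ SD, so I assume normal LAZ with SD from 0.9 to 1.3, anchored on the plan's 40% below −2. The mean is then −2 + 0.2533 × SD. F is the resulting distribution function and g a gain common to all children.

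- Stunted: failure share = F(−2 − g) / F(−2)
- At risk: failure share = [F(−1 − g) − F(−2)] / [F(−1) − F(−2)]

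Setting each share to 0.20 and solving for g:

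| SD | Stunted (3 months) | At risk (2 months) |
|---|---|---|
| 0.9 | 1.04 Z | 0.82 Z |
| 1.0 | 1.15 Z | 0.81 Z |
| 1.2 | 1.38 Z | 0.81 Z |
| 1.3 | 1.50 Z | 0.80 Z |

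**3. Failure share at smaller assumed gains.** With SD 1.0 and a common gain:

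| Gain | Stunted failing | At risk failing |
|---|---|---|
| 0.1 Z | 90% | 92% |
| 0.2 Z | 81% | 83% |
| 0.3 Z | 72% | 73% |
| 0.5 Z | 56% | 53% |

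Across SD 0.9–1.3, mean gain 0.1–0.5 Z and SD of individual change 0–0.4, the share runs from about 51% to 93% over the two cohorts. Per 525 recruits:

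- failures: 525 × 0.51 ≈ 268 to 525 × 0.93 ≈ 488, against 105
- consenters at one-third: about 89 to 163, against 35
- recruits that would yield 105 failures: 105 / 0.93 ≈ 113 to 105 / 0.51 ≈ 206, against 525

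Consenters are counted before the exclusions for secondary causes, celiac disease and clotting disorders, for which the documents give no usable rate.

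**4. Both definitions in one population.** Let individual gains be normal with exactly 20% not improving, as the Sample size section words it (LAZ SD 1.0, SD of change 0.2–0.5, hence mean gain 0.17–0.42 Z). Under the rule in use, 63–83% of stunted and 57–83% of at-risk children then fail, and 65–76% of those failures have improved.

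**5. Adults.** Failure needs both clauses. Reaching BMI 18.5 from entry value b takes a relative gain of 18.5/b − 1, which is below 10% whenever b > 18.5/1.10 = 16.8. For entry BMI of about 16.8–18.5, anyone still under 18.5 has necessarily gained less than 10%, so the change clause adds nothing. At entry BMI 18.4 a gain of 0.5% ends failure (18.5/18.4 = 1.005). The documents give no BMI distribution or expected gain, so no adult failure rate can be computed.

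**The case against.** The strongest reply is that the Sample size section restates the 20% as failing to respond, which is the term the endoscopy section defines, and that the article discloses that the criterion was assumed for want of data. The disclosure is fair, but it concerns the criterion. It does not tell the reader that the rate is first worded for a different event, and under the rule in use 20% sits badly with incremental improvement.

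Four stronger readings are tempting, and the documents do not support them.

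- *The sample-size chain is broken.* It is arithmetically sound; one input is unsupported.
- *The biopsy target is at risk.* The probable error gives more candidates, and 35 and 105 are stated as minimums. Nor is the excess recruitment shown to be wasted, since the 525 per cohort also serve the before-and-after biomarker measurements, the biomarker–growth models and the celiac screening of 1575.
- *Non-responder mostly means started far below the line.* This depends on an unstated SD of change. Among stunted children in the model of step 4, failure correlates −0.45 with baseline and −0.37 with change when that SD is 0.2, but −0.50 and −0.57 when it is 0.5. The order also reverses in at-risk children, who start at most 1 Z below their line.
- *The growth analyses are corrupted by the label.* The Data analysis plan names no responder analysis; it correlates scores and biomarkers with anthropometric changes.

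It also stands that every failure share above rests on assumed normality, SD and gain.

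**Conclusion.** The concern holds at moderate severity. For both child cohorts, the rate that sizes recruitment and the rule that identifies failures describe different events. That follows from the text alone and needs no model.

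Its size does depend on assumptions. Under those in the working, 20% failure would take gains of about 1.0–1.5 Z (stunted) or 0.8 Z (at risk), while mean gains of 0.1–0.5 Z imply about 50–93% failure. That is roughly 270–490 failures and 90–160 consenters per 525 before exclusions. The consequences are a misstated expected number of endoscopy candidates, a misstated recruitment need, and a biopsied group that would include many children who improved.

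For adults the finding is narrower. Linear growth cannot describe their 20%, and their change clause is inactive over entry BMI of about 16.8–18.5, so that figure needs a stated basis too.

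**What to change.** Reconcile the Sample size section with the definitions of failure to respond, so that the assumed rate and the rule describe the same event. Then restate, separately for each cohort and with a range, the expected failures, consenters and recruitment figure under the rule actually used, giving the assumed LAZ or BMI distribution and gain. Which eligibility rule for endoscopy is kept is for the investigators.

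State that the failure label serves only to describe who was offered endoscopy. Keep the growth analyses on change in LAZ (BMI in adults), as the Data analysis plan already indicates, adjusted for baseline value. The repeated measurements in Table 4 ("Anthropometry done fortnightly") already supply the data.

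The cost is revised planning text and a clarifying sentence on analysis. No new data are needed, though the 20% and the 525 become less neat.

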### Dietary supplementation

Supplementation (table 1) of the usual home diet with one boiled egg and 150 mL of whole milk provide an additional 745 kilojoules, 11.1 g of protein and 11.5 g of fat to the daily diet of enrolled subjects. The duration of the intervention is 3 months for the stunted cohort and 2 months for those who are at risk for stunting and malnourished adults. Egg and milk were selected considering the nutritional values and the fact that they have shown acceptable to the target population in a small pilot study. Multiple studies have found significant positive effects of egg and milk on linear growth.^8–10^

Nutritional therapy is delivered between the morning and midday meal, anytime between 10:00 am to 11:30 am to avoid the food substitution. Participants are asked to come to the designated nutrition centre daily for their nutritional therapy in order to avoid the issue of food sharing with other family members. A staff member visits the family’s household if a participant defaults in coming to the nutrition centre. Study co-investigators also visit nutrition centres regularly to monitor food left over, absenteeism and other issues of compliance.

We assume that this regimen of food supplementation plus counselling will result in incremental improvement in linear growth of participant children. A participant is discontinued from the study and referred for medical evaluation if he/she shows reluctance to feed for 7 consecutive days, which includes daily intake of ≤50% of the offered food.

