### Challenges

Several questions arose in the development and implementation of the BEED study, all of which were brought to the Investigators’ Committee for discussion and resolution. For example, AEs that may arise during endoscopy were a big concern and to solve the issues, investigators have developed a priori definitions, assessment criteria and action guidelines. Morbidity and poor appetite also represent a big challenge; by providing proper counselling and by practising supportive feeding techniques, this issue can be resolved.

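### The poor-feeding rule discontinues participants from the study, which conflicts with assessing all enrolled participants for response and may cause informative loss in the biomarker-growth analyses

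*Protocol article*

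**What the plan says.** **The rule.** Protocol article, Dietary supplementation: "A participant is discontinued from the study and referred for medical evaluation if he/she shows reluctance to feed for 7 consecutive days". The criterion is completed by "which includes daily intake of ≤50% of the offered food". The object is the study, not the supplement. The article mentions no later sampling, no route back and no analysis status for these participants.

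**Response assessment.** The section on indications for endoscopy states: "After completion of nutritional therapy, all enrolled participants are assessed for responses".

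**Timing of the data.** Study settings and participants, in the text after Figure 1: "Candidate EED biomarkers are being measured in faeces, urine and plasma samples collected from participants once before and once after the nutritional intervention". The same text gives the route to histology: "Participants who fail to respond to nutritional therapy are considered eligible for UGI endoscopy with mucosal biopsies". Table 4 places the second blood, stool and urine collection and the final anthropometry at the post-intervention assessment.

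**Sample size.** The formula is defined so that "n is the required sample size without attrition". The later steps allow for non-response to nutrition and for refusal of endoscopy, but not for discontinuation.

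**Challenges.** "Morbidity and poor appetite also represent a big challenge". The same sentence goes on to say that counselling and supportive feeding can resolve this.

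**The concern.** The rule is triggered by low intake during the intervention. Low intake is plausibly tied to illness: the rule itself sends these participants for medical evaluation, and the Challenges section names morbidity and poor appetite together. It is also plausibly tied to growth, because the Dietary supplementation section assumes that the food is what improves linear growth.

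The Data analysis plan relates biomarker levels to anthropometric change. A participant removed from the study before the post-intervention visit has no second biomarker value and no final LAZ or BMI. If such participants differ systematically from the rest, the biomarker-growth associations are estimated in a sample that has lost people for a reason connected with growth. An analysis plan cannot recover samples that were never taken.

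There is also a plain inconsistency about who is assessed for response, and the stated number of biopsies leaves no room for any loss.

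**Working it through.** **1. The two sections side by side**

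- If the response assessment covers everyone enrolled, it contradicts a rule that removes some of them from the study beforehand.
- If it covers only those who complete therapy, the contradiction goes, but the post-intervention data of discontinued participants are then certainly not collected.

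The article does not say which is meant.

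**2. What is lost and what is kept under the literal rule**

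- Lost: post-intervention anthropometry; the second stool, urine and blood biomarkers; entry to the endoscopy pathway.
- Kept: pre-intervention samples; fortnightly anthropometry up to discontinuation; the record of food offered, consumed and left over (Data collection, management and storage).

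**3. The plan's own figures, reproduced**

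Inputs from Sample size: z = 1.96, P = 0.9, d = 0.1, non-response about 20%, consent to endoscopy one-third.

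- n = z² × P × (1 − P) / d² = 1.96² × 0.9 × 0.1 / 0.01 = 34.57, rounded up to 35.
- 35 × 3 = 105 non-responders; 105 / 0.20 = 525 recruited per cohort; 3 × 525 = 1575 in total.
- Backwards: 525 × 0.20 / 3 = 35.0. There is no slack.

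**4. Effect of discontinuation on the cascade**

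The article gives no rate, so 2, 5 and 10% are assumptions. With discontinuation unrelated to response:

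- expected biopsies = 525 × (1 − rate) × 0.20 / 3
- recruitment that restores 35 = 525 / (1 − rate), rounded up
- half-width at P = 0.9 is 1.96 × √(0.09 / biopsies)

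| Assumed rate | Expected biopsies per cohort | Recruitment to restore 35 | Half-width |
|---|---|---|---|
| 0% | 35.0 | 525 | 9.9 points |
| 2% | 34.3 | 536 | 10.0 points |
| 5% | 33.25 | 553 | 10.2 points |
| 10% | 31.5 | 584 | 10.5 points |

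**5. Sensitivity if the loss is related to response**

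Suppose, as a further assumption, that would-be non-responders are three times as likely to be discontinued. Their rate is then 3 × rate / (0.2 × 3 + 0.8) = 3 × rate / 1.4, which is 4.3, 10.7 and 21.4% for overall rates of 2, 5 and 10%.

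- Non-responders left: 105 × (1 − that rate) = 100.5, 93.75 and 82.5.
- Expected biopsies, dividing by 3: 33.5, 31.25 and 27.5.
- Observed non-response, dividing by the 514.5, 498.75 and 472.5 remaining: 19.5, 18.8 and 17.5% instead of 20%.

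These figures show direction and scale only. Neither the rate nor the threefold ratio comes from the article. The bias in a biomarker-growth association cannot be computed at all from what is given.

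**The case against.** Several parts of the case on the other side stand.

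- **Biopsy.** Endoscopy is for those who fail nutritional therapy. A participant who did not eat the food has not clearly failed it, so keeping such participants out of biopsy is defensible. Continued non-invasive follow-up adds no biopsies and does not repair the count of 35.
- **Frequency.** A reader might infer from the Challenges section that poor appetite is expected to be common. The section gives no frequency and says the issue can be resolved.
- **Selection.** A reader might infer that the sample is selected on the outcome, or that the severe end of EED is cut off and the biomarker-histology correlations weakened. The rule selects on intake, not on LAZ, BMI or histology. A link from intake to EED is plausible but undocumented, and the biopsied group is already selected by design on non-response, exclusion of secondary causes and consent. No figure for a distorted EED share can be derived from the article.
- **Size.** Even 10% loss unrelated to response moves the planned half-width only from 9.9 to 10.5 points.
- **Safeguards.** Defaulters are visited at home, intercurrent illness is treated, and the early data are kept.
- **Condensed article.** The full protocol or the Manual of Procedures may say what happens to data collection after the rule is met.

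The last point does not dispose of the matter. The article does not merely leave the handling open. It says discontinued from the study in one section and all enrolled in another. Nor does the defence of excluding these participants from biopsy explain why their scheduled anthropometry and stool, urine and blood samples should end.

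**Conclusion.** The point holds in a limited form. Two sections disagree about who is assessed after therapy and must be reconciled. Under the literal feeding rule, post-intervention anthropometry and biomarkers are missing for participants whose poor intake is plausibly related to illness and growth, so the biomarker-growth analyses may be affected by informative loss. That rests on plausibility, not on data in the article, and its size is unknown.

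The cascade from 525 to 35 has no allowance for this loss. Any discontinuation takes the expected biopsies below 35 per cohort, unless non-response or consent turns out higher than assumed. With 2 to 10% loss unrelated to response the shortfall is 0.7 to 3.5 biopsies, which is modest. The article does not support a stronger conclusion that the histology findings are biased.

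**What to change.** Leave the feeding-related clinical rule and the referral as they are. Then:

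1. Reconcile Dietary supplementation with the section on indications for endoscopy, so that it is clear whether participants who meet the rule are assessed after therapy. If the full protocol already settles this, bring the article's wording into line with it.
2. State that, where consent continues, the non-invasive post-intervention assessment already in Table 4 (anthropometry, stool, urine, blood) is still done for these participants.
3. Report the number discontinued under the rule in each cohort.
4. Show the biomarker-growth analyses with and without these participants.
5. Say under Sample size that 525 per cohort makes no allowance for this loss and that the expected biopsies fall below 35 per cohort if any occurs, with the assumed rate stated.

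The cost is a short amendment and one already scheduled visit for what should be a few participants. Some may decline it, so the loss would be reduced and not removed. The article reports enrolment ongoing in May 2017 and expected to continue until December 2018, so at the time of writing much of this could still be collected.
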